#### Study Comparison

Results from the centers will be compared with their own results in the preintervention period using data collected for the ITS study.

#### Outcomes Measured

Our primary outcome will be a hospital-level composite outcome of 30-day hospital readmission and ED visit rate. Our secondary outcomes will be hospital-, clinical-, and patient- or caregiver-level outcomes (Table 1).

#### Hospital-Level Outcomes

Hospital administrative databases (eg, Med-GPS, Logibec) will be used to calculate monthly hospital-level outcomes. Monthly data will then be analyzed to form points in time. Data will be extracted from the *Régie de l’assurance maladie du Québec* (RAMQ) physician billing database and Maintenance et exploitation des données pour l'étude de la clientèle hospitalière (Med-ECHO) database (containing data on hospitalizations and health professional consultations for all institutions) in addition to databases available at the INESSS in order to identify all public health services used prior to and after the implementation of the CISSS-CA ACE program.

#### Patient- and Caregiver-Level Sociodemographics and Outcomes

Patient and caregiver baseline sociodemographic data will include age, sex, race, language, education level, family income, prehospital living situation (eg, home, intermediate nursing homes, etc), geography of residence (rural vs urban: as defined by Statistics Canada for Rural and Small Town [81,82]), and reason for hospital admission or consultation in the ED. Patient and caregiver outcomes are presented in Table 1. The living situation will be noted in the medical file when available at 30 days after discharge. Other measures that will be collected after discharge include the Care Transitions Measure-3 (CTM-3) [17,83], the Geriatric Anxiety Inventory-Short Form (GAI-SF) [84,85], and the Zarit Burden Interview (ZBI) [86]. The CTM-3 is a three-item questionnaire that measures the perceived quality of care transition on a 0-4 scale (0, fully disagree; 4, fully agree). The French version of the tool will be used [87]. The GAI-SF measures anxiety among seniors. The short version comprises five questions. The French-Canadian version of the tool has good psychometric properties [88]. The ZBI measures the burden of caregivers. The brief French version (12 questions) of the scale has good psychometric properties and is comparable to the original version [89,90].

#### Clinical-Level Process Outcomes

In order to measure the change in care processes, we will measure process outcomes such as the proportion of patients seen by the GEM nurse, proportion of patients having a medication reconciliation list, and proportion of patients receiving telemonitoring services (Table 1).

#### Patient and Caregiver Recruitment

After receiving ethics approval, we will start recruitment for our patient-level outcomes at least 3 months before the implementation of phase 1A at each site. Due to the pragmatic nature of our study, some sites will have longer periods of patient-level outcomes collected before phase 1A than others. Patient recruitment will continue throughout our study and up to a maximum of 24 months after the intervention. We will recruit consecutive eligible ED patients aged 65 years or older, as well as one caregiver whenever possible. We will recruit 38 patients or caregivers per month for each of the four hospitals based on a precision estimate of the CTM-3 measured for the study point of each month.

With authorization from the Director of Nursing and the Professional Services Director, a member of our embedded research team will contact by telephone a randomly selected daily sample of patients who visited the ED in the last 24 hours and up to a maximum of 7 days after their ED visit. This research assistant will administer the CTM-3 questionnaire to patients for quality improvement purposes. The research assistant will then ask the patients if they agree to be contacted a second time by a member of the research team to answer additional questions for the purpose of our study. Consenting patients will then be contacted within 7 days to obtain their verbal consent to participate in the study and consent to access their medical charts. We will ensure patients’ understanding by asking them to summarize in their own words the objectives of the study and what their participation involves using the Nova Scotia criteria [91]. The team member will then collect baseline sociodemographic data and administer the questionnaires for the study. The research team will then send a written consent form by mail after the interview. If a patient refuses to be contacted by our research team or to participate in this study, the CTM-3 data collected will only be available to the CISSS-CA. The research assistant will also ask permission to contact a caregiver. Identified caregivers will be contacted by telephone to complete the Zarit questionnaire. Our research assistant will first obtain the caregivers’ verbal consent to participate in the study and then ensure the caregivers’ understanding by asking them to summarize in their own words the objectives of the study and what their participation implies.

#### Sample Size and Statistical Analysis

We will use segmented regression statistics to measure the changes in the level and slope in the postintervention period compared with the preintervention period in each center for each of our primary and secondary outcomes [92]. Thus, we will present a regression model with different intercept and slope coefficients for the pre- and postintervention time periods for each center. We will compare the changes in a composite primary outcome (total 30-day hospital readmission and ED visit rate) at our four intervention centers. We will use a Durbin-Watson test to verify the presence of autocorrelation and use an autoregressive error model to correct for this serial correlation. For an ITS, 10 measurement points before and 10 points after an intervention provide 80% power to detect a change in the level of 5 standard deviations (of the predata) only if the autocorrelation is greater than 0.4 (ie, extent to which data collected close together in time are correlated with each other) [93].

We have calculated the sample size for our patient cohort, which will be based on the smallest clinically significant difference (ie, 11%) that the CTM-3 can capture on a maximum score of 100. To detect a difference of 11% with a type I error of 5% and a type II error of 20%, 38 patients per month are needed to calculate a monthly CTM-3 estimate, based on a previous study in which CTM-3 was measured in 21 patients at Hôtel-Dieu Hospital in Lévis and showed an average of 75% and a standard deviation of 23%. Considering a call rejection rate of 70%, the number of people to be contacted in total will be 127 patients per month for each ED. We will therefore contact 5 patients per day in each of the four participating centers to obtain our targeted sample size of 38 patients at the end of the month. To ensure the creation of a random and representative sample of our population of elderly patients being discharged from the ED, a randomization table based on all patients discharged in the previous 24 hours from the ED will be provided every day to select which patients to call.

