## Methods

### Study Design

Our study will have two main parts (Figure 1). Part 1 will involve the staggered implementation of the context-adapted CISSS-CA ACE program across four CISSS-CA sites (Hôtel-Dieu de Lévis, St-Georges, Montmagny, and Thetford Mines). We will use an interrupted time series (ITS) to measure the impact of the CISSS-CA ACE program and its context-adapted tools on all hospital-level outcomes (Table 1 and Figure 2). This design will allow us to better measure the effect of our intervention on our outcomes while controlling for secular trends in our data by comparing retrospective monthly data collected in the CISSS-CA administrative databases for 36 months before our intervention and for a maximum of 12 months after our intervention in the last targeted CISSS-CA implementation site (Hospital 4 is yet to be determined) and for up to 21 months in the first targeted CISSS-CA implementation site (Hospital 1 is the Hôtel-Dieu de Lévis). Part 2 will be a parallel mixed-methods process evaluation study to understand the underlying human, organizational, and technical factors that influence the success or failure of our intervention and, more specifically, of our Wiki-suite to facilitate it through the adaptation and uptake of geriatric knowledge tools. We will report this implementation study using the Standards for Reporting Implementation Studies (StaRI) reporting guidelines (Multimedia Appendix 1) [71]. This study has been approved by the CISSS-CA Ethics Review Committee (project #2018-462, 2018-007).

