#### Phase ID (Implementation, 9 Months)

In the 9 months following training and local adaptation, we will implement the context-adapted CISSS-CA ACE program with the support of WikiTrauma and local implementation teams who will have the responsibility to roll out the different elements of our intervention within their respective hospitals. Our context-adapted CISSS-CA ACE program will include a series of systematic predischarge, postdischarge, and across transition period interventions for eligible patients as follows: (1) screening of patients in need of multidimensional evaluation of their loss of autonomy (with the *Programme de Recherche sur l’Intégration des Services de Maintien de l’Autonomie 7* [PRISMA-7] tool) [76]; (2) a geriatric emergency management (GEM) nurse; (3) geriatric training [77]; (4) communication tools for transmitting information to nursing homes and other community-based stakeholders in the health system; (5) a fall prevention program; (6) systematic medication reconciliation; (7) elder-friendly ED environment adaptation; (8) access to clinician- and patient-centered Wiki-based KT tools [78,79] (eg, standing orders for geriatric patients admitted to the ED, geriatric analgesia prescription order set, and patient communication tools and decision aids); and (9) access to a community-based telemonitoring service. This service, which is offered by *Télé-Surveillance Santé - Chaudière-Appalaches* (TSS-CA) [80], will be offered for free to all eligible patients (ie, patients aged over 65 years who have at least seven ED visits in last 12 months, where over half of these visits are triaged to the ED observation unit and where two visits are not followed by hospitalization) transitioning from the hospital or ED to their home. This service currently offers remote monitoring of patients; nurses available 24 hours a day, 7 days a week, 365 days a year; and monthly phone check-ups. It also includes a customized emergency response intervention when patients are in need and connects patients with a network of community-based volunteer caregivers who are notified to visit patients when in need or simply to conduct a routine check-up.

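### If process proportions start low, a segmented regression with one residual variance misstates the standard error of the slope change when the pre and post segments differ in length

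*Protocol article*

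**What the plan says.** Under Sample Size and Statistical Analysis, the protocol article says: "We will use segmented regression statistics to measure the changes in the level and slope in the postintervention period compared with the preintervention period", and this applies "in each center for each of our primary and secondary outcomes". The form is given as "we will present a regression model with different intercept and slope coefficients for the pre- and postintervention time periods for each center". Residuals are checked with a Durbin-Watson test, and where needed the authors will "use an autoregressive error model to correct for this serial correlation". No link function, weighting or variance function is mentioned.

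The secondary outcomes in Table 1 include clinical-level process measures. The section on them lists "proportion of patients seen by the GEM nurse, proportion of patients having a medication reconciliation list, and proportion of patients receiving telemonitoring services". GEM-nurse contact and reconciliation come from chart audit, receipt of the discharge summary from phone contact, and telemonitoring from a service database. Two of these measures are also components of the program: Phase ID introduces "a geriatric emergency management (GEM) nurse" and systematic medication reconciliation.

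On series length, Study Design gives 36 retrospective months of administrative data before the intervention. Follow-up afterwards runs "for a maximum of 12 months after our intervention in the last targeted CISSS-CA implementation site", and up to 21 months in the first. Patient-level recruitment starts at least 3 months before Phase IA, with longer lead-ins at some sites, and runs up to 24 months after the intervention. Prospective collection runs from January 2019 to January 2022.

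**The concern.** A monthly proportion from n patients has variance p(1-p)/n. A measure that the program itself introduces can be expected to start low and then rise, so its monthly points scatter little before implementation and much more after it. Durbin-Watson and an autoregressive error model deal with correlation between months. They do not deal with a change in variance between segments.

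If both segments share one residual variance, the quiet segment lends its precision to the noisy one, or the reverse, and the number of months in each decides which. The estimated slope change remains unbiased, but its confidence interval and p value do not mean what they say. That matters because the slope change is the term that shows whether uptake of a component grows or fades within a hospital after the start.

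**Working it through.** **Inputs.**
- Patients per month: 38, the CTM-3 target. A one-sample calculation with difference 11, SD 23, two-sided 5% and 80% power gives (1.96 + 0.84)² × 23²/11² ≈ 35 by the normal formula and 37 by the exact t. That is close to the stated 38, and 38/(1 - 0.70) = 127 matches the stated number to contact. Applying 38 to the audited charts is an assumption. It is reasonable because chart access needs patient consent, and actual enrolment was 1635/(4 × 12) ≈ 34 per hospital-month.
- Series length: January 2019 to January 2022 is about 36 months. With a common start, 36 - 12 = 24 months before (24/12) and 36 - 21 = 15 before (15/21). The split is assumed, not stated.
- Baseline p0 and post-start p1: not in the article, so varied below.

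**Formula.** Each segment has its own intercept and slope, so the slope change is the difference of two separate slopes. With S = n(n² - 1)/12 for a segment of n months:
- true variance = v0/S0 + v1/S1
- pooled variance = s²(1/S0 + 1/S1), with s² = [(n0 - 2)v0 + (n1 - 2)v1]/(n0 + n1 - 4)

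**Numbers for p0 = 5%, p1 = 50%.** v0 = 0.05 × 0.95/38 = 0.00125; v1 = 0.25/38 = 0.00658.
- 24/12: S0 = 1150, S1 = 143. True SE = √(0.00125/1150 + 0.00658/143) = 0.00686. s² = (22 × 0.00125 + 10 × 0.00658)/32 = 0.00292, so pooled SE = √[0.00292 × (1/1150 + 1/143)] = 0.00479. The SE is too small: ratio 0.70.
- 15/21: S0 = 280, S1 = 770. True SE = 0.00361. s² = (13 × 0.00125 + 19 × 0.00658)/32 = 0.00441, pooled SE = 0.00464. The SE is too large: ratio 1.29.
- Equal lengths: s² = (v0 + v1)/2 and S0 = S1, so the two variances coincide and the error cancels.

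**Simulated rejection rates.** 20,000 series per setting; flat before, step, flat after; independent months; ordinary least squares; nominal 5%. For the slope, these are false positives. For the level, they are rejections of the true step.

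| p0 to p1 | slope, 24/12 | slope, 15/21 | level, 24/12 | level, 15/21 |
|---|---|---|---|---|
| 2% to 50% | 21.5% | 1.0% | 14.9% | 2.2% |
| 5% to 50% | 16.9% | 1.5% | 12.0% | 2.5% |
| 10% to 50% | 12.3% | 2.2% | 9.5% | 3.2% |
| 20% to 50% | 8.0% | 3.6% | 7.1% | 4.0% |
| 40% to 60% | 5.1% | 5.3% | 5.2% | 4.7% |

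The level columns come from a repeat run, whose slope figures agreed with those shown to within about half a percentage point.

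**Other checks.**
- An autoregressive fit triggered by Durbin-Watson leaves the 24/12 slope figures at 20.6% (p0 = 2%) and 17.3% (p0 = 5%).
- Separate pre and post variances bring all the slope figures in these two layouts to 4.7-5.3%.
- For p0 of 0.1-5%, 12/12 gives 5.6-6.5% and 24/24 gives 5.1-5.5%.
- 36 months before, the administrative-data layout, gives 22-34% at 36/12 and 14-20% at 36/21.

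**The case against.** The strongest objection is that constant variance is inferred. The article does not say ordinary least squares, normal errors or unweighted fitting, and it excludes neither a binomial model nor robust errors. It is a condensed account, and such details usually sit in an analysis plan that is not shown. Study Design also ties the time series to hospital-level outcomes. This stands in part. But the statistical section explicitly covers every secondary outcome in each center, and the tools it names are those of linear regression on a monthly series. The point is therefore about a stated choice, conditional on how it is carried out.

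Second, no baseline proportion is given. A low start is plausible for GEM-nurse contact and uncertain for reconciliation or discharge summaries. Telemonitoring is described as an existing service. Earlier ACE work took place at the first hospital, so its baselines may be higher. This stands, and it is why the size is shown as a range.

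Third, the simulation steps up at once, whereas Phase ID is a 9-month roll-out. Under gradual uptake a true slope exists and rejecting is no false positive. That stands too, but the standard error would still be wrong.

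A reader might infer fixed error rates for particular hospitals: inflation at the last and almost none at the first. The documents do not support that. The pre-period for chart-audit outcomes is not fixed, the contrast vanishes at 12/12 or 24/24, and with 36 months before at both sites both are inflated. Nor do they support calling a between-hospital comparison an artefact. Each center is compared with its own past, a comparison across centers is named only for the primary outcome, and implementation is compared by case study.

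**Conclusion.** The concern holds conditionally. The plan puts process proportions under the same segmented regression as everything else and names no remedy except for autocorrelation. If a proportion starts low and rises, and one residual variance is used, the slope-change test is invalid when the segments differ in length. It rejects too often when the post segment is much the shorter (about 17-21% at 24/12 for baselines of 2-5%) and too rarely when the post segment is the longer (about 1% at 15/21). At a 10% baseline the figures are about 12-13% and 2%, and at 20% about 8% and 4%. With equal lengths or a change from 40% to 60%, little or nothing is left.

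These figures rest on 38 audited patients per month, binomial variation only, independent months, an immediate step to 50% and a common 36-month window. The primary outcome is not part of this point. The calculation also gives no ground for changing how CTM-3, GAI-SF or ZBI monthly means are analyzed.

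**What to change.** For outcomes that are monthly proportions from chart audit or phone interview, state that the segmented model is fitted to the monthly numerator and denominator, with binomial variance and an overdispersion term. Alternatively, keep the linear model and allow separate residual variances before and after the start. Keep the autocorrelation check in either case. Where every pre month is zero, report only the level and slope after the start.

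The cost is a sentence or two of analysis text and slightly more programming, with no new data. The article says analysis has not yet begun, so the change can still be made in advance. One limit applies: separate variances are themselves unreliable with very few pre months. With 3, simulated false positives ran from about 4% to 12%.

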#### Study Intervention

Our intervention is the delivery of a context-adapted CISSS-CA ACE program using a KT strategy based on our Wiki-suite. This intervention will be deployed in sequential phases.

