A PhD student guided by experienced qualitative researchers will perform the interviews and process evaluation of our intervention. For this analysis, we will perform a mixed inductive and deductive qualitative content analysis of the verbatim transcripts and field notes taken during these interviews, as well as key implementation project documents such as executive committee and local team meeting minutes [94,96]. The analysis will involve reading the verbatim transcripts and key project documents thoroughly and developing codes that represent the nature of the implementation, adaptation processes at each site, and barriers and facilitators to using our context-adaptation methodology. Our previous experience in conducting qualitative content analysis about Wiki use will help us understand how our Wiki-based intervention succeeded (or not) in improving care transitions [70]. We will use the Ottawa Model for Research Use [97] and the KTA framework [98] to structure our analysis.

We will also use the National Health Service (NHS) Sustainability Model to guide our process evaluation analysis [99]. The NHS Sustainability Questionnaire has been developed to support health care leaders to implement and sustain effective improvement initiatives in health care systems. The questionnaire is a diagnostic tool that identifies strengths and weaknesses in the implementation plan and predicts the likelihood of sustainability for improvement initiatives. The NHS Sustainability Questionnaire will be administered to members of the executive committee and each local implementation team at baseline before phase IA and at regular 3-month periods until 12 months after the end of phase ID.

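### A one-break level-and-slope model is planned for a program rolled out over 9 months, so neither coefficient measures the full-implementation effect and the centres' coefficients are not comparable

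*Protocol article*

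**What the plan says.** Sample Size and Statistical Analysis states the model: "we will present a regression model with different intercept and slope coefficients for the pre- and postintervention time periods for each center". It adds: "We will compare the changes in a composite primary outcome (total 30-day hospital readmission and ED visit rate) at our four intervention centers". No phase-in term is named.

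Study Intervention says of the program: "This intervention will be deployed in sequential phases". Phases IA, IB and IC are local set-up, training and tool adaptation, 3 months each. Phase ID then takes 9 months: "In the 9 months following training and local adaptation, we will implement the context-adapted CISSS-CA ACE program". It has nine listed components, and the section on Phase IA identifies Phase ID as the active implementation.

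Study Design gives the series as monthly data "for 36 months before our intervention and for a maximum of 12 months after our intervention in the last targeted CISSS-CA implementation site", with up to 21 months after at the first site. The text does not tie that time origin to the start or end of a phase. Limitations says the interrupted time series will be used only if descriptive statistics show a clear inflection that coincides with implementation. Study Comparison says each centre is compared with its own earlier results.

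**The concern.** A two-segment model is right when the intervention switches on in one month. Here the article describes elements being added over 9 months. If the effect builds up with them, a straight line with a jump at the start cannot follow a curve that rises and then levels off. The level change understates the full effect, and the slope change suggests improvement that continues after the program is complete.

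How the effect is split between the two terms also depends on how many months follow the break. The centres have different post-windows by design, so an identical program effect would yield different coefficients at each. A reader who sets the four centres side by side could take that difference for a difference in success. Within one centre, neither coefficient answers the question of how far the composite rate moved once the program was in place.

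**Working it through.** **Plan's own figure.** The article gives none for this point. Its one time-series figure is a power statement about a level change and plays no part here.

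**Inputs from the article.** 36 pre-months; 12 or 21 post-months, taken at their maxima (Study Design); 9 months of roll-out (Phase ID); separate intercept and slope before and after (Sample Size and Statistical Analysis).

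**Assumptions.** The break is the start of Phase ID. The true effect is e(k) = D(k+1)/9 for k = 0 to 8 and D afterwards, where k = 0 is the first post-month. There is no noise, and errors are independent.

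**Share of the last site's window that is roll-out.** 9 of 12 months, leaving 12 − 9 = 3 at full implementation.

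**Method.** The two segments have separate lines and the effect is zero before the break, so the level and slope changes are the least-squares line of e(k) on the n post-months. The length of the pre-period does not matter.

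- slope = [Σk·e(k) − n·k̄·ē] / Σ(k − k̄)²
- level = ē − k̄·slope
- fitted effect in the twelfth month = level + 11·slope

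**12 post-months.** ē = (5 + 3)/12 = 0.667D. k̄ = 5.5 and Σ(k − k̄)² = 143. Σk·e(k) = 240/9 + (9 + 10 + 11) = 56.67D.
- slope = (56.67 − 44)/143 = 0.0886D per month
- level = 0.667 − 5.5 × 0.0886 = 0.18D
- twelfth month = 0.179 + 11 × 0.0886 = 1.15D (true value 1.00D)

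**21 post-months.** ē = (5 + 12)/21 = 0.810D. k̄ = 10 and Σ(k − k̄)² = 770. Σk·e(k) = 240/9 + 174 = 200.67D.
- slope = (200.67 − 170)/770 = 0.0398D per month
- level = 0.810 − 10 × 0.0398 = 0.41D
- twelfth month = 0.411 + 11 × 0.0398 = 0.85D (true value 1.00D)

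**Sensitivity of the level change (break at the start of Phase ID).**

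| Assumption | 12 post-months | 21 post-months |
|---|---|---|
| Immediate effect | 1.00D | 1.00D |
| 3-month ramp | 0.72D | 0.83D |
| 6-month ramp | 0.39D | 0.60D |
| 9-month ramp (above) | 0.18D | 0.41D |
| 12-month ramp | 0.08D | 0.26D |
| Three 3-month steps | 0.35D | 0.55D |
| 9-month ramp coded k/9 | 0.04D | 0.29D |
| 9-month ramp, AR(1) errors, ρ = 0.2 | 0.18D | 0.39D |
| 9-month ramp, AR(1) errors, ρ = 0.6 | 0.15D | 0.27D |

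In every gradual case the shorter follow-up gives the smaller level change, and both fall short of D. The model is correct only for an immediate effect.

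**Check on handling the roll-out.** Leaving out the 9 Phase ID months and reading the level at month 9 gives 1.00D with zero slope change at both lengths of follow-up. The distortion therefore comes from how the roll-out months are treated.

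**The case against.** The strongest reply has four parts.

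*The comparison is within centre.* Study Comparison sets each centre against its own past, and no formal between-centre test of coefficients is stated. This stands: a reader might infer such a test from the sentence on the four centres, but the text does not require one. The within-centre problem remains, because neither coefficient at any one centre is the full-implementation effect.

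*The slope is reported too.* The effect is reallocated between terms and not lost: the fitted mean effect equals the true mean, 0.667D and 0.810D. That is true, but combining level and slope at month 12 still gives 1.15D or 0.85D where the truth is 1.00D.

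*The figures are one scenario.* This stands, and the table shows how far they move. The article states no ramp shape.

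*Phase-in coding and site dates may sit in a fuller document.* Their absence alone would not be a finding, and Figure 1 (the study timeline) was not available for this review. But the article does state a model form, and that form does not fit the intervention it describes.

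A reader might also see a conflict between "for a maximum of 12 months after our intervention in the last targeted CISSS-CA implementation site", the 21 months at the first site, and patient recruitment "up to a maximum of 24 months after the intervention". The text does not support that. These are maxima for different data streams: monthly administrative data and patient recruitment. Data collection from January 2019, plus 3 months' lead and 9 months of preparation, allows Phase ID to start as early as January 2020. That leaves 24 months to January 2022, enough for all three windows.

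**Conclusion.** The point holds as a worthwhile improvement. A model with one break is stated for a program that the same article describes as phased in over 9 months, with unequal post-windows. If the effect builds up with the roll-out and the break is the start of Phase ID, the level and slope changes depend on ramp shape and follow-up length. The example of 0.18D and 0.41D rests on a linear 9-month ramp, maximum follow-up and independent errors; the plausible range is wide.

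Three stronger readings should not be drawn:

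- *An 18-month roll-out.* The phases total 3 + 3 + 3 + 9 = 18 months, but only the last 9 are active implementation. An 18-month linear ramp would give 0.06D and 0.08D, with almost no contrast between sites.
- *A level change that mostly reflects follow-up length.* With 12 post-months, ramp length moves it from 0.72D to 0.08D, more than follow-up moves it for a 9-month ramp (0.18D to 0.41D).
- *A level change of the wrong sign.* Values of −0.07D and −0.25D arise only if the break is put at the start of Phase IA, which is set-up and not active implementation.

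**What to change.** - Set the break in advance at each site's Phase ID start, taken from the implementation log and not from an inflection seen in the data.
- Code exposure through Phase ID as the proportion of roll-out completed, from 0 to 1.
- Code Phases IA to IC as a separate preparation segment, or exclude them in a sensitivity analysis.
- Make the primary contrast at each centre the modelled rate minus the counterfactual at a common time, for example 12 months after Phase ID start.

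The cost is analysis wording and additional design columns. Results says data analysis has not begun, so the change can be made before outcomes are examined. There are two downsides. The result will depend on the assumed roll-out coding, so an alternative coding should be shown. If IA to IC are excluded, 9 months per site no longer inform the contrast. Dropping the Phase ID months altogether is not advised: it removes the distortion in principle but leaves only 3 post-months at the last site.
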